### Stratification and randomization

Patient randomization will be performed using a secure online computer randomization system, either directly in the operating room or by the trial coordinator via phone. Block randomization will be employed to ensure balanced participant numbers throughout the trial. Stratification will be applied based on the following factors: age (younger or older than 70 years), tumor stage, gender, ASA classification (1–2 vs. 3), presence of small bowel distention, and study center. Randomization must be completed within 24 h of study enrollment. Treatment allocation will not be concealed from patients, physicians, or researchers at any point during the trial.

After obtaining preoperative informed consent, patients will be randomly assigned in a 1:1 ratio to the trial. The choice of the surgical technique (minimally invasive vs. open) and the method of reconstruction (primary anastomosis or discontinuous resection) during tumor resection, as well as the type of stoma (loop ileostomy, loop colostomy or cecal fistula) in the bridge-to-surgery group is at the discretion of the surgeon.

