### Statistics

The statistical analysis plan for the study involves various tests and methods to analyze different endpoints. The chi-squared test will be applied to compare the perioperative 120-day mortality between the control and intervention arms using an intent-to-treat analysis. The significance levels were set to 5% (two-sided). The secondary endpoints will each be analyzed accordingly: The rate of primary anastomoses, permanent stomas, and 120-day complication rate will be investigated using the chi-square test. The 3-year overall survival will be examined using the Kaplan-Meyer estimator combined with the log-rank test. The treatment effect on the patient-reported quality of life will be analyzed using a regression analysis. Quality-adjusted survival will be analyzed using marginal models and non-parametric regression.

The statistical significance of stratification factors will be assessed. Propensity score matching may be used as a part of a supplementary analysis, to control for potential confounding factors that were not accounted for during sampling. In particular, a propensity score matching procedure with age as a continuous variable may be used to control for between-arm age differences. Statistical analyses of matched-sub-cohorts will have an exploratory character, providing additional information about effect sizes. The standardized mean differences and confidence intervals will be reported, and *p*-values will be provided as an additional information.

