### Sample size calculations

The sample size calculation was performed using an estimated 120-day mortality rates of 8% and 1.7% in the control and intervention arms, respectively. These rates were extrapolated from the 90-day mortality rates of 1.7% (decompressing stoma (DS)) vs 7.2% (emergency resection (ER)) as well as the 3-year overall survival data in the propensity-score matched study by Veld, Tanis et al. [18]. The effect size was then reduced with an assumed 120-day mortality rate of 1.7% for the decompressing stoma group and 7% in the emergency resection group, resulting in a reduced effect size of 0.274 and an increased relative risk of 0.243.

To achieve the 80% power with a (two-sided) 5% significance level using a normal curve via arcsine transformation (Cohen, 1988, Chapter 6), at least 210 patients per arm (total 420 patients) need to be analyzed. To account for an expected 10% dropout rate, the target enrollment is 468 patients (234 per arm). Considering a 20% screen-failure rate, 588 patients will need to be assessed for eligibility. The power calculations were performed using SAS Version 9.4.

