### Methods against bias

To address potential bias and ensure the integrity of the study, several methods have been implemented. As mentioned above, randomization and stratification will be used to allocate patients into the control and intervention groups. This process will be conducted using a secure online computer randomization system and will consider factors such as age, tumor stage, gender, ASA classification, presence of small bowel distention, and study center. By stratifying these variables, a balanced distribution can be achieved, reducing the risk of bias. To account for the delay between decompressing stoma placement and tumor resection in the intervention group, the primary endpoint of perioperative mortality has been adjusted to 120-day. This extension allows for a comprehensive evaluation of mortality rates in both groups with an appropriate timeframe.

The primary endpoint will be analyzed using the intention-to-treat (ITT) principle, and the final study report, in line with transparent reporting standards, will adhere to the CONSORT (Consolidated Standards of Reporting Trials) statement.

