### Criteria for discontinuing the study

The following termination rules or criteria are applicable:Individual patient termination: In the event that a patient, who has previously undergone a decompressive stoma procedure within the intervention group, becomes medically ineligible for the subsequent two-stage operation, their informed consent will be withdrawn.Exclusion of participating investigative centers: Investigative centers that deviate from the study protocol, primarily due to inadequate patient recruitment (less than one per year) and compromised data quality, will be excluded from the analysis.Study suspension: The entire study will be temporarily suspended following the occurrence of any of the subsequent events until evaluated by the data and safety monitoring board (DSMB):Elevated incidence of severe morbidity and/or postoperative mortality observed within either the intervention or control groupIncreased frequency of surgical interventions within either the intervention or control groupReceipt of a recommendation from the DSMB to prematurely terminate the study due to participant safety concerns in either of the two groups

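### Dropping under-recruiting or poor-data centres from the analysis contradicts the promised intention-to-treat primary analysis, and the data-quality ground for doing so is undefined

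*Protocol article*

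**What the plan says.** Under Criteria for discontinuing the study, the protocol article lists a rule for centres that depart from the protocol. Such centres, "primarily due to inadequate patient recruitment (less than one per year) and compromised data quality, will be excluded from the analysis". The exclusion is mandatory, and it is from the analysis, not only from further enrolment. Nothing limits it to a per-protocol or sensitivity set.

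Two other sections fix the primary analysis differently. Statistics says the chi-squared test will "compare the perioperative 120-day mortality between the control and intervention arms using an intent-to-treat analysis". Methods against bias repeats: "The primary endpoint will be analyzed using the intention-to-treat (ITT) principle".

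On blinding, Stratification and randomization says: "Treatment allocation will not be concealed from patients, physicians, or researchers at any point during the trial".

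**The concern.** Closing a poorly performing centre to new patients is ordinary trial management. Removing patients it has already randomised is a post-randomisation exclusion, which intention-to-treat is meant to rule out. As written, the primary analysis population depends on which section the analyst follows.

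The two grounds for exclusion carry different risks. The recruitment ground is a count, does not depend on arm or outcome, and by construction touches only very small centres. The data-quality ground is a judgement. The article gives no threshold for it, no time by which it must be made, and no one shielded from allocation to make it. It could also remove a large centre. Since allocation is open and the endpoint is death, nothing in the text prevents the judgement from being made by someone who knows which arm would gain.

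**Working it through.** **1. The plan's sample size (Sample size calculations).** Inputs: 7% against 1.7% mortality, two-sided 5% level, 80% power, arcsine method.

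- Effect size h = 2·asin(√0.07) − 2·asin(√0.017) = 0.274, as stated.
- n per arm = 2 × ((1.960 + 0.842)/0.274)² = 209.07, rounded up to 210, as stated.
- With 10% dropout, 210/0.9 = 233.3, rounded up to 234 per arm and 468 in total, as stated.
- Power at 210 per arm = Φ(h·√(210/2) − 1.960) = 80.2%.

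**2. Which centres the recruitment ground can reach.** There are 66 committed hospitals (Feasibility of the recruitment), and recruitment runs from October 2023 to about October 2026 (Trial status). The mean is 468/66 = 7.1 patients per centre, or 2.4 per centre-year. A centre open for all 3 years and recruiting below one a year has at most 2 patients.

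**3. How many randomised patients that discards.** The article gives no distribution of recruitment over centres, so this is an assumption. Expected patients lost = 66 × [P(1) + 2·P(2)], with mean 7.09 per centre.

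| Assumed recruitment | Centres with 1-2 patients | Patients discarded |
|---|---|---|
| Equal rates (Poisson) | 1.8 | 3.2 |
| Gamma-Poisson, shape 3 | 8.8 | 13.9 |
| Gamma-Poisson, shape 2 | 10.8 | 16.6 |
| Gamma-Poisson, shape 1.5 | 12.1 | 18.3 |
| Gamma-Poisson, shape 1 | 13.4 | 19.7 |

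The range is about 3 to 20 patients.

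**4. Effect on power.** Taking the loss straight from the 420 to be analysed:

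- 3 patients: 208.5 per arm, power 79.9%.
- 14 patients: 203 per arm, power 78.8%.
- 20 patients: 200 per arm, power 78.2%.

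Taking 20 from the 468 enrolled and then applying 10% dropout gives 448 × 0.9/2 = 201.6 per arm and power 78.6%.

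**5. How fragile the result is.** Expected deaths are 210 × 0.07 = 14.7 and 210 × 0.017 = 3.6, about 18 in all. The uncorrected chi-squared test with 210 per arm gives:

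| Deaths, emergency resection vs stoma | p |
|---|---|
| 15 vs 4 | 0.010 |
| 14 vs 4 | 0.016 |
| 13 vs 4 | 0.026 |
| 12 vs 4 | 0.041 |
| 11 vs 4 | 0.066 |

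Starting from the design expectation, four control-arm deaths must go before significance is lost. Starting from 12 vs 4, one is enough.

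**6. Deaths among patients lost on the recruitment ground.** At the average design rate of (7% + 1.7%)/2 = 4.35%, 14 to 20 patients contain about 0.6 to 0.9 deaths.

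**7. The data-quality ground.** No calculation is possible. The article gives neither a criterion nor a limit on centre size, so the number of patients and deaths at risk cannot be bounded.

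**The case against.** The strongest reply is that the practical effect is small and largely neutral. Whole centres go, both arms together. Allocation is 1:1 and centre is a stratification factor, so the recruitment ground has no evident tendency to favour one arm. It costs at most 1 to 2 points of power, and only under an assumed spread of recruitment. The two grounds are joined by *and*; if both must hold, only very small centres are affected. The full protocol or an analysis plan, neither of which is shown, may set timing and criteria.

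Most of this stands and limits the size of the point. It does not remove the contradiction: on either reading of the conjunction, randomised patients leave an analysis described as intention-to-treat. The article states the exclusion outright, so this is not a detail left for later. An analysis plan that kept these patients would contradict the rule.

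A reader might infer more than the document supports:

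- **That the primary comparison will be biased, or that centres will be excluded with outcomes known.** The article says neither. It fails to prevent selective exclusion, which is a weaker statement.
- **That small recruiters have worse emergency-resection results, so excluding them shifts the effect.** Nothing in the article says so, and recruitment into the trial is not surgical volume. The lead department sees 15-20 such patients a year and expects to include about 10.
- **That the loss falls outside the 10% dropout allowance.** The article does not define what dropout covers.
- **That losing one or two deaths would overturn the result.** At the design rates it takes four. One or two matter only if the result is already borderline.

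**Conclusion.** Wrong as written. The centre-exclusion rule and the intention-to-treat primary analysis cannot both be carried out, and this conclusion needs no assumed figure.

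The recruitment ground is a minor loss of precision: about 3 to 20 patients, with power between 79.9% and about 78%. That rests on all 66 centres being open for 3 years and on the assumed recruitment distributions. The larger exposure is the data-quality ground, whose reach cannot be bounded from the document. With about 18 deaths expected and allocation open, an unblinded and undefined exclusion could settle a borderline result. The case for changing the rule rests on this open discretion and on the contradiction, not on a demonstrated bias.

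**What to change.** Replace the centre rule with wording such as: *Centres with inadequate recruitment or data quality are closed to further recruitment; all patients already randomised there continue follow-up and are included in the ITT analysis.*

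Allow the exclusion of centres with confirmed data-integrity problems only as a sensitivity analysis, with those centres identified by people blind to arm and outcome.

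The cost is a short protocol amendment, which by the article's own rule needs prior ethics approval and a note in the registry, and continued vital-status follow-up at closed centres. The sample size stays at 210 analysed and 234 enrolled per arm. The change should be made before any centre is excluded.

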### Protocol changes

Modifications to the study protocol will only be made upon obtaining prior approval from the ethical committee. Any protocol changes will be duly noted on the German Clinical Trials Register (DRKS).

### Dissemination trial results

The results will be submitted to the German Clinical Trials Register (DRKS) and published in a peer reviewed journal. Furthermore, the patient group ILCO which was involved in defining the primary and secondary endpoints of the study will be used to disseminate the results among its members.

## Discussion

Colorectal cancer represents the third leading cause of cancer death in Europe and the USA. The risk increases with age, with more than half of the patients diagnosed above the age of 70. Acute colonic obstruction is a common presentation, accounting for up to 30% of cases, and represents one of the most common causes of surgical emergency. While the preferred treatment for obstructing right-sided colon cancers is primary resection with an ileocolic anastomosis, there is a lack of consensus regarding the optimal approach for left sided obstructive colon cancer [4], which accounts for two thirds of all colon cancers [23]. Primary resection with or without anastomosis is the most recommended procedure according to international guidelines, although bridge-to-surgery treatment is also considered. Emergency resection carries a higher risk of morbidity and mortality, while the bridge-to-surgery approach has the potential for resection and intermediate metastasis.

A recent large retrospective study utilizing data of the Dutch Colorectal Audit (DCRA)—a national mandatory registry—suggests that the bridge-to-surgery approach can significantly reduce perioperative mortality and permanent stoma rates and improve long-term survival in patients with left-sided obstructive colon cancer [18]. However, retrospective studies have limitations in accurately representing the interval between stoma creation and resection. Furthermore, existing prospective studies are either very outdated [16] or involve a comparison between endoscopic stenting and emergency resection in a relatively small number of patients [24]. Endoscopic stenting in obstructive cancer is technically challenging with a limited success rate of 78% in highly specialized centers. This high level of endoscopic expertise is not available in most hospitals where patients with acute obstructive colon cancer present themselves. Additionally, concerns regarding microperforations during stenting and their impact on long-term oncological outcomes exist. Nevertheless, these studies have shown an increased rate of primary anastomoses and a significant reduction in permanent stomas.

To address these uncertainties, the present study aims to compare the peri- and postoperative outcomes of patients with obstructive left-sided colon cancer who undergo emergency resection versus those who receive decompressing stoma as bridge-to-surgery. The objective is to determine the optimal approach for the treatment of obstructive left-sided colon cancer and shed light on the associated perioperative and long-term outcomes.

## Trial status

COMPASS is currently establishing recruitment sites and is expecting to begin recruitment in October 2023. The current protocol version is 2.0F. The approximate end date for recruitment will be October 2026.

## Data Availability

The data that support the findings of this study are available from the corresponding author upon reasonable request.
